Visit three will occur three weeks later. In between visits two and three, participants will be asked to record their habitual diet and activity for three days, which will be used to assess any between-group differences. For each subsequent assessment day, participants will be prescribed a standardised breakfast to consume at home 3 hours prior to attending the laboratory. Otherwise, participants will be instructed to consume their habitual diet and, during each laboratory visit, a 24-hour dietary recall will be conducted to assess any changes in dietary intake. Participants will be instructed to abstain from the use of non-steroidal anti-inflammatory drugs, strenuous exercise, engagement in massage or cryotherapy, and the consumption of alcohol, protein supplements, vitamin and mineral supplements, and ergogenic aids during the study period.

Upon arriving at the laboratory for the third visit (pre), a trained phlebotomist will collect a venous blood sample in three vacutainers; one containing a serum separator (8.5 mL); and two containing no reagent (10 mL) (28.5 mL total). Following blood collection, the participants' limb circumference of the thigh will be measured with a standard measuring tape and their limb range of motion will be assessed with a goniometer. Muscle soreness will be measured by use of a visual analogue scale (VAS) questionnaire while performing a standard bodyweight squat, and the pressure-pain threshold (PPT) test using a standard pressure algometer. Participants will then perform a single bout of resistance exercise at their allocated load intensity, firstly on the leg press and secondly, on the leg extension, separated by five-minutes rest. The exercise protocol will consist of a warm-up set (10 repetitions at 50% of the participants pre-established 1RM), followed by three sets performed to volitional failure (when a full repetition can no longer be completed) at either 30% or 80% 1RM. Two-minutes of rest will be awarded between each set of exercise and the participants will be verbally encouraged throughout.

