Immediately following the exercise bout (post), another venous blood sample will be taken (3 x 8.5-10 mL) and the measures of limb circumference, range of motion, and muscle soreness will be repeated. Then, participants will be provided a dairy yoghurt containing 20 g of milk protein to stimulate muscle repair and growth. These four measures (excluding protein consumption) will be repeated during the morning of visits four (+24 h), five (+48 h), six (+72 h), and seven (+168 h). Also, during visits six and seven, the 1RM strength test will be repeated on the leg press and leg extension. Over the experimental period, a total of 171 mL of blood will be collected from each participant. This is the equivalent of ~34 teaspoons and is a common amount obtained during exercise physiology research. The blood samples will be used to analyse serum concentrations of creatine kinase, myoglobin (markers of muscle damage), C-reactive protein, and interleukin-6 (markers of inflammation).

**OBJECTIVE 2/PART B:** This study will employ a randomised parallel groups design, for which 22 healthy females aged 18-35 years will be recruited. Prior to the first laboratory visit, prospective participants will have the opportunity to ask questions and gain further information about the study via a video/phone call with the lead researcher. If willing to participate, participants will be asked to electronically sign a consent form. Participants will be asked to record their menstrual cycle and inform the lead researcher at the onset of menses – this information will be used to arrange the time of the baseline assessments, as all measures will be conducted during the late follicular phase of the menstrual cycle.

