For the first visit, which acts as a familiarisation session, participants will arrive at the laboratory in the morning and be screened for eligibility with a standard health and readiness to exercise questionnaire. Next, participants will be familiarised with the exercise equipment and demonstrated correct form. Then, participants' maximal strength will be estimated through a one repetition maximum (1RM) test on the leg press and leg extension machines. Approximately three days later, participants will return to the laboratory and a baseline assessment of body composition will be conducted using dual energy X-ray absorptiometry (DXA). The 1RM test will be repeated on the leg press and leg extension machines for confirmation of maximal strength. Participants will then be randomly assigned to either a protein or placebo group. The protein group will be consuming a whole-food source of milk protein (dairy yoghurt) providing 20 g of milk protein and the placebo group will consume a carbohydrate-based food source that contains the

same amount of calories.

Visit three will occur three weeks later. In between visits two and three, participants will be asked to record their habitual diet and activity for three days, which will be used to assess any between-group differences. For each subsequent assessment day, participants will be prescribed a standardised breakfast that will contain either the protein or placebo product to consume at home 3 hours prior to attending the laboratory. Participants will consume one dose of their allocated supplement in the laboratory after exercise and be given a further two doses to consume at home interspaced by four hours. Therefore, 4 doses of the supplement will be consumed in each 24-hour period for four consecutive days, though on the final testing day, only one dose will be consumed with breakfast (17 doses total). Otherwise, participants will be instructed to consume their habitual diet, and during each laboratory visit a 24-hour dietary recall will be conducted to assess any changes and between-group differences in dietary intake. Participants will also be instructed to abstain from the use of non-steroidal anti-inflammatory drugs, strenuous exercise, engagement in massage or cryotherapy, and the consumption of alcohol, additional protein supplements, vitamin and mineral supplements, and ergogenic aids during the study period.

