#### 4. RISKS AND ETHICAL ISSUES

#### RESEARCH PARTICIPANTS

**A17-1. Please list the principal inclusion criteria (list the most important, max 5000 characters).**

Males and females (PART A)  
Females-only (PART B)

All other inclusion criteria apply to PART A and PART B:

Aged 18-35 years

BMI 18.5 -25.0 kg/m^2

Untrained in resistance exercise

No known chronic disease or current acute illness

No current or recent (past 3 months) musculoskeletal injury

No frequent use (2x per week for past month) of non-steroidal anti-inflammatory drugs and compliant to abstain from use during experimental period

No recent or current engagement in massage or cryotherapy and compliant to abstain from use during experimental period

No current use of protein or antioxidant supplements

Females will be eumenorrheic >12 months

Absence of pregnancy and breast-feeding

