**A17-2. Please list the principal exclusion criteria (list the most important, max 5000 characters).**

<18 years or >35 years of age

Underweight

Overweight/obese

Resistance trained

Current or recent injury

Pregnancy or breast-feeding

Lactose intolerant

Unwilling to provide blood samples, perform resistance exercise, or abstain from use of NSAID's and protein supplementation (unless instructed as part of the research)

Unwilling to abstain from other forms of exercise during the experimental period

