**RESEARCH PROCEDURES, RISKS AND BENEFITS**

**A18. Give details of all non-clinical intervention(s) or procedure(s) that will be received by participants as part of the research protocol. These include seeking consent, interviews, non-clinical observations and use of questionnaires.**

Please complete the columns for each intervention/procedure as follows:

1. Total number of interventions/procedures to be received by each participant as part of the research protocol.
2. If this intervention/procedure would be routinely given to participants as part of their care outside the research, how many of the total would be routine?
3. Average time taken per intervention/procedure (minutes, hours or days)
4. Details of who will conduct the intervention/procedure, and where it will take place.

| Intervention or procedure                    | 1  | 2 | 3      | 4                                                                                                                                   |
|----------------------------------------------|----|---|--------|-------------------------------------------------------------------------------------------------------------------------------------|
| Obtaining informed consent                   | 2  | 0 | 5 mins | [name];
Human Performance Laboratory, Durham University                                                                   |
| General demographic and health questionnaire | 2  | 0 | 5 mins | Completed by the participant in the presence of [name];
Human Performance Laboratory, Durham University                   |
| Readiness to exercise questionnaire          | 2  | 0 | 5 mins | Completed by the participant in the presence of [name];
Human Performance Laboratory, Durham University                   |
| Habitual diet and activity record            | 2  | 0 | 3 days | [name] will give instruction on how the record should be completed and then the participant will complete the record at home |
| 24-hour dietary recall                       | 10 | 0 | 5 mins | [name];
Human Performance Laboratory, Durham University                                                                   |
| Measurement of maximal leg strength          | 8  | 0 | 45     | [name];                                                                                                                      |

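### NSAIDs are the only pain medicine participants must avoid and no painkiller use is recorded after exercise, so soreness-driven use could weaken the soreness and pain-threshold comparisons unseen

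*Protocol*

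**What the plan says.** **Restrictions.** For Part A, section A13 states: "Participants will be instructed to abstain from the use of non-steroidal anti-inflammatory drugs, strenuous exercise, engagement in massage or cryotherapy". The same sentence goes on to bar alcohol, supplements and ergogenic aids. For Part B: "Participants will also be instructed to abstain from the use of non-steroidal anti-inflammatory drugs", followed by a near-identical list. Inclusion (A17-1) requires "No frequent use (2x per week for past month) of non-steroidal anti-inflammatory drugs and compliant to abstain from use during experimental period". Exclusion (A17-2) covers people unwilling to "abstain from use of NSAID's and protein supplementation". No other pain medicine is mentioned anywhere.

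**Pain outcomes.** A13 says: "Muscle soreness will be measured by use of a visual analogue scale (VAS) questionnaire while performing a standard bodyweight squat". A pressure-pain threshold test by algometer accompanies it. Both are taken before and immediately after exercise and at +24, +48, +72 and +168 h, in both parts.

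**What is recorded between visits.** At each laboratory visit "a 24-hour dietary recall will be conducted to assess any changes in dietary intake"; the Part B wording is also confined to diet. The three-day diet and activity record falls between visits 2 and 3, before the exercise bout. The health and readiness questionnaires are screening tools at visit 1. The form's own question A18 reads "Give details of all non-clinical intervention(s) or procedure(s) that will be received by participants as part of the research protocol", and its table contains no medication log or painkiller question.

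**Ice.** A6-2 and A22 advise ice, among other measures, for bruising from the algometer. A13 and A17-1 require participants to abstain from cryotherapy.

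**The concern.** The protocol already treats relief of soreness as a contaminant, since it bars NSAIDs, massage and cryotherapy. Non-NSAID painkillers (paracetamol, for example) are left open, and use of any kind is left unmeasured. Breaches of the NSAID rule would go unseen too.

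Participants spend the days of peak interest at home. Those who hurt most have most reason to take something. Relief lowers the VAS score and raises the pain threshold, so use that tracks soreness acts hardest on the group with more damage. The contrasts between loads, sexes and diets would then be pulled towards zero. A null soreness result could not be separated from one masked by painkillers, and no later analysis plan can recover use that was never recorded.

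**Working it through.** **Plan's own figures.** There is none for soreness, pain threshold or analgesic use. The sample size (A60) rests on muscle strength with no standard deviation given, so it does not bear on this point.

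**Coverage check.** Each place where post-exercise use might be captured:

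| Instrument | When | Covers painkillers after exercise? |
|---|---|---|
| Health and readiness questionnaires | Visit 1 | No, before exercise |
| Diet and activity record | Between visits 2 and 3 | No, before exercise |
| 24-hour dietary recall | Laboratory visits | Diet only |
| Other A18 rows | Various | No medication item |

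The recall's window is also short. Between visits 6 and 7 there are 168 − 72 = 96 h, of which a 24-hour recall spans the last quarter.

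**Illustration 1: proportional relief.** All inputs are assumptions; the documents give none. True mean VAS is S1 = 50 mm in the sorer group and S2 = 35 mm in the other. Use is u1 = 20% to 40% against u2 = 10%. The score is lower by e = 15% to 30% when a remedy is used.

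Observed difference = S1(1 − u1·e) − S2(1 − u2·e)

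| u1 | u2 | e | Calculation | Observed (mm) | Shrinkage from 15 mm |
|---|---|---|---|---|---|
| 0.20 | 0.10 | 0.15 | 50 × 0.970 − 35 × 0.985 | 14.03 | 7% |
| 0.30 | 0.10 | 0.30 | 50 × 0.910 − 35 × 0.970 | 11.55 | 23% |
| 0.40 | 0.10 | 0.30 | 50 × 0.880 − 35 × 0.970 | 10.05 | 33% |

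The span over the assumed ranges is 7% to 33%. Algebraically the difference shrinks whenever S1·u1 exceeds S2·u2. With equal use it shrinks by the factor (1 − u·e): at u = 20% and e = 30%, 15 × 0.94 = 14.1 mm. With these means it would not shrink if the less sore group used remedies at 50/35 = 1.43 times the rate of the sorer group, or more.

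**Illustration 2: additive relief.** Let d0 be the standardised difference that gives 80% power in an independent two-sided t-test at 0.05, a the relief in SD units, and f the excess share of users in the sorer group. Then d = d0 − a·f. Again a and f are assumptions.

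| a | f | Part B, 9 v 9 (d0 = 1.407): share kept, power | Part A loads, 16 v 16 (d0 = 1.024): share kept, power |
|---|---|---|---|
| 0.25 | 0.1 | 98%, 79% | 98%, 78% |
| 0.50 | 0.3 | 89%, 71% | 85%, 67% |
| 1.00 | 0.5 | 64%, 44% | 51%, 30% |

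The shrinkage is 2% to 49%. With f = 0 the mean difference does not change in this model. The two models differ on equal use, which shows how far the size depends on assumptions.

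**Scale.** With 9 completers per group, 10% against 40% use is about 1 user against 4 (0.9 and 3.6). A handful of people would be enough.

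**The case against.** - **The document is an ethics form.** A13 asks for a lay summary and A17 for the most important criteria only, so silence is weak evidence. A painkiller question could be asked within the recall without its own row. This has some force, but A18 asks for all procedures, including questionnaires, and itemises tasks as short as five minutes. The stated purpose of the recall is diet.
- **NSAIDs are far from the only restriction.** This is correct. Massage, cryotherapy, strenuous exercise, alcohol and supplements are barred too. The point is confined to pain medicines and to the absence of any record of use.
- **Handling of affected readings belongs in a statistical analysis plan.** That is true of the analysis. It is not true of data collection, which must be fixed before the first exercise bout.
- **Differential use is presumed.** Every group exercises to volitional failure, and A12 cites studies that found no load difference in damage. Which group is sorer is the research question. This stands: direction and size are both conditional.
- **Reach is limited.** Soreness is one domain beside blood markers, circumference, range of motion and strength, and the sample size rests on strength. This stands. Under the mechanism described, the bias is also towards zero, so it would not produce a false positive.

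A reader might infer that sorer participants will take other painkillers and that the soreness results are therefore biased. The documents do not support that. They contain no usage rate, analgesic effect or soreness level, and equal use with additive relief leaves the mean difference unchanged.

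**Conclusion.** The gap is real but modest. NSAIDs are the only pain medicine restricted, and no listed procedure would reveal use of any painkiller or soreness remedy after exercise, including NSAID breaches and ice. If use follows soreness, the load, sex and diet differences in VAS soreness and pressure-pain threshold are attenuated invisibly. The 7% to 33% span illustrates the mechanism under assumed VAS inputs and is not an estimate; the additive model spans 2% to 49%. Neither gives a figure specific to pressure-pain threshold. Creatine kinase, myoglobin, C-reactive protein and interleukin-6 are not clearly affected. This is a cheap improvement worth making, because it decides whether a small or null soreness difference can be interpreted. It does not undermine the trial as a whole.

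**What to change.** 1. At visits 4 to 7, alongside the dietary recall, ask about any painkiller or soreness remedy since the last visit (product, time, amount). Include NSAID breaches and ice. Add the item to A18.
2. Report use by group (load, sex, diet) and time point. This is the core of the remedy: if use is rare or balanced, the soreness result is better protected; if it is uneven, readers can see it.
3. As a sensitivity analysis, repeat the VAS and pressure-pain threshold comparisons in a mixed model with readings taken shortly after such use set to missing, and define that interval beforehand. State that this assumes those readings are missing at random given the participant's other readings. That is open to doubt when unusually high soreness prompted the use. Replacing them with each group's worst observed value is not advisable: the value depends on the outcome, differs between groups and can overshoot the true difference.
4. Reconcile the advice to use ice on bruising (A6-2, A22) with the bar on cryotherapy (A13, A17-1). Which should stand, and whether the abstention list changes, is for the investigators.

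The cost is one question at four existing visits and one extra analysis, which will have little precision in groups this small.

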#### 4. RISKS AND ETHICAL ISSUES

#### RESEARCH PARTICIPANTS

**A17-1. Please list the principal inclusion criteria (list the most important, max 5000 characters).**

Males and females (PART A)  
Females-only (PART B)

All other inclusion criteria apply to PART A and PART B:

Aged 18-35 years

BMI 18.5 -25.0 kg/m^2

Untrained in resistance exercise

No known chronic disease or current acute illness

No current or recent (past 3 months) musculoskeletal injury

No frequent use (2x per week for past month) of non-steroidal anti-inflammatory drugs and compliant to abstain from use during experimental period

No recent or current engagement in massage or cryotherapy and compliant to abstain from use during experimental period

No current use of protein or antioxidant supplements

Females will be eumenorrheic >12 months

Absence of pregnancy and breast-feeding

**A17-2. Please list the principal exclusion criteria (list the most important, max 5000 characters).**

<18 years or >35 years of age

Underweight

Overweight/obese

Resistance trained

Current or recent injury

Pregnancy or breast-feeding

Lactose intolerant

Unwilling to provide blood samples, perform resistance exercise, or abstain from use of NSAID's and protein supplementation (unless instructed as part of the research)

Unwilling to abstain from other forms of exercise during the experimental period

**RESEARCH PROCEDURES, RISKS AND BENEFITS**

**A18. Give details of all non-clinical intervention(s) or procedure(s) that will be received by participants as part of the research protocol. These include seeking consent, interviews, non-clinical observations and use of questionnaires.**

Please complete the columns for each intervention/procedure as follows:

1. Total number of interventions/procedures to be received by each participant as part of the research protocol.
2. If this intervention/procedure would be routinely given to participants as part of their care outside the research, how many of the total would be routine?
3. Average time taken per intervention/procedure (minutes, hours or days)
4. Details of who will conduct the intervention/procedure, and where it will take place.

| Intervention or procedure                    | 1  | 2 | 3      | 4                                                                                                                                   |
|----------------------------------------------|----|---|--------|-------------------------------------------------------------------------------------------------------------------------------------|
| Obtaining informed consent                   | 2  | 0 | 5 mins | [name];
Human Performance Laboratory, Durham University                                                                   |
| General demographic and health questionnaire | 2  | 0 | 5 mins | Completed by the participant in the presence of [name];
Human Performance Laboratory, Durham University                   |
| Readiness to exercise questionnaire          | 2  | 0 | 5 mins | Completed by the participant in the presence of [name];
Human Performance Laboratory, Durham University                   |
| Habitual diet and activity record            | 2  | 0 | 3 days | [name] will give instruction on how the record should be completed and then the participant will complete the record at home |
| 24-hour dietary recall                       | 10 | 0 | 5 mins | [name];
Human Performance Laboratory, Durham University                                                                   |
| Measurement of maximal leg strength          | 8  | 0 | 45     | [name];                                                                                                                      |

|                                                                                              |    |   |         |                                                                                                                       |
|----------------------------------------------------------------------------------------------|----|---|---------|-----------------------------------------------------------------------------------------------------------------------|
|                                                                                              |    |   | mins    | Human Performance Laboratory, Durham University                                                                       |
| Measurement of muscle soreness by pressure algometry and visual analogue scale questionnaire | 12 | 0 | 15 mins | [name];
Human Performance Laboratory, Durham University                                                     |
| Measurement of leg range of motion by goniometry                                             | 12 | 0 | 5 mins  | [name];
Human Performance Laboratory, Durham University                                                     |
| Measurement of leg circumference by standard tape measure                                    | 12 | 0 | 5 mins  | [name];
Human Performance Laboratory, Durham University                                                     |
| Completion of a leg-based resistance exercise protocol                                       | 2  | 0 | 30 mins | [name];
Human Performance Laboratory, Durham University                                                     |
| Ingestion of milk protein (yoghurt) or carbohydrate-based placebo (Part B only)              | 17 | 5 | 5 mins  | [name] will provide the milk protein for the participants to consume either at the laboratory or at their home |

**A19. Give details of any clinical intervention(s) or procedure(s) to be received by participants as part of the research protocol.** *These include uses of medicinal products or devices, other medical treatments or assessments, mental health interventions, imaging investigations and taking samples of human biological material. Include procedures which might be received as routine clinical care outside of the research.*

Please complete the columns for each intervention/procedure as follows:

1. Total number of interventions/procedures to be received by each participant as part of the research protocol.
2. If this intervention/procedure would be routinely given to participants as part of their care outside the research, how many of the total would be routine?
3. Average time taken per intervention/procedure (minutes, hours or days).
4. Details of who will conduct the intervention/procedure, and where it will take place.

| Intervention or procedure                                                             | 1  | 2 | 3       | 4                                                                 |
|---------------------------------------------------------------------------------------|----|---|---------|-------------------------------------------------------------------|
| Assessment of body composition by dual energy X-ray absorptiometry                    | 3  | 0 | 20 mins | [name];
Truscott Imaging Suite, Durham University       |
| Note: 2 scans for part A and 1 scan for part B                                        |    |   |         |                                                                   |
| Venous blood sampling by venepuncture (28.5 mL per sample; 342 mL total)              | 12 | 0 | 15 mins | [name];
Human Performance Laboratory, Durham University |
| Note: 6 samples for part A (171 mL) and 6 samples for part B (171 mL) of the research |    |   |         |                                                                   |

